### Posttest Care Provisions

Once the study is completed, as this is a low-intervention trial, posttrial care is not required that differs from standard clinical practice. In this case, if the participant quits smoking, he/she will be discharged from the SCU; if not, he/she will remain a patient in the SCU, and an alternative smoking cessation treatment (change of intervention format or combination of drugs) will be considered.

### Outcomes

A full set of outcomes will be analyzed to obtain clinical information on efficacy, safety, and economic impact of maintained cytisinicline therapies versus the standard cytisinicline regimen. Outcomes are classified into efficacy, safety, and economic evaluation objectives.

### Specific Outcomes Efficacy

Different outcomes will be used to measure the efficacy of cytisine in each arm of the clinical trial.

The sustained abstinence rate will be determined in each of the three treatment arms at 6 and 12 months, based on carbon monoxide co-oximetry results in ppm. The correlation between the sustained abstinence rate in each of the three arms studied at 6 and 12 months, based on co-oximetry results, and the self-reported abstinence at 6 and 12 months will be calculated.

Additionally, point abstinence will be analyzed every 7 days in each of the 3 arms studied, based on the results obtained in the CO tests.

The percentage increase in abstinence rates will be compared with the increase in the duration of cytisinicline use. The number needed to quit smoking for one patient in each treatment group will also be calculated.

Interval abstinence will also be determined in this clinical trial. The abstinence rate will be analyzed from Day 25 to Day 50 in all 3 study groups and from Day 25 to Day 75 in all 3 study arms. The abstinence rate will also be determined from Day 25 (usual arm), Day 50 (extended arm 1), and Day 75 (extended arm 2) up to 6 and 12 months.

Relapse rates will be analyzed in each treatment arm. The frequency and percentage of relapses will be determined in those who quit smoking from Day 25 (usual arm), Day 50 (extended arm 1), and Day 75 (extended arm 2) up to 6 and 12 months in all 3 arms.

Craving and withdrawal symptoms will be assessed during the clinical trial. The mean Minnesota Nicotine Withdrawal Scale (MNWS) score and the mean craving score will be calculated at the initial in-person visit in all 3 arms, and their change from this visit will be measured on days 25, 50, and 75 in all 3 study arms.

Predictors of continued abstinence at 6 and 12 months of treatment and of relapse (clinical, anthropometric, demographic, and smoking-related variables) will be determined in all study arms.

Quality of life in each group will be calculated using the EQ-5D-5L scale score at baseline, 50 days, 90 days, 6 months, and 1 year.

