### Schedule of Participants

Table 3 and Figure 1 show the screening visit, follow-up visits (face-to-face and telephone), tests and quizzes to be carried out at each of the visits, and the interventions.

**Table 3 table3:** Visiting calendar. The screening visit, follow-up visits (face-to-face and telephone), tests and quizzes to be carried out at each of the visits, as well as the intervention.

Number, day, and type of visit		Visit 1 (day 1; in person)		Visit 2 (day 7; in person)		Visit 3 (day 14; telephone)		Visit 4 (day 21; in person)		Visit 5 (day 25; telephone)		Visit 6 (day 50; telephone)		Visit 7 (day 75; telephone)		Visit 8 (day 90; in person)		Visit 9 (day 120; in person)		Visit 10 (day 150; in person)		Visit 11 (week 24; in person)		Visit 12 (week 36; telephone)		Visit 13 (week 48; in person)		Visit 14 (week 52; in person)			

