Other qualities of the smoker, such as the degree of motivation and self-efficacy, will be evaluated by the Analogue Visual Scale. This scale numerically identifies a smoker’s level of motivation and self-efficacy to quit smoking. A score above 7 indicates high motivation and self-efficacy to quit smoking [27].

The EQ-5D scale will be used in this clinical trial to assess the quality of life of smokers and its changes during the smoking cessation process. This scale measures the health status of smokers using 5 dimensions, including mobility, self-care, activities of daily living, pain and discomfort, and anxiety and depression. Participants score from 0 to 100 in each domain [31].

The urge to smoke in this study will be analyzed using the Craving Rate Score. This scale assesses anxiety or intense desire to smoke at baseline and during follow-up. It is scored from 0 to 4 [32].

The additional tests that will be performed on smokers participating in this trial include electrocardiogram, carbon monoxide levels, complete blood count, and a biochemical profile that includes liver enzymes, electrolytes, and renal function tests. Co-oximetry allows for the objective identification of smoking status, as well as confirmation of abstinence at each participant visit. A participant is identified as a nonsmoker when their CO levels measured by co-oximetry are below 10 ppm (Textbox 2).

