### Limitations

This study is not placebo-controlled; therefore, the effect of the intervention (extended cytisinicline treatment) cannot be accurately determined. The results of the intervention could be attributed not only to the drug but also to external factors. However, the use of a placebo could compromise the low level of intervention in this trial, according to regulatory authorities in Spain and the European Union. Furthermore, the synthesis of the placebo would hinder the feasibility of this study. Also, not including a placebo in the 25-day and 50-day treatment arms could provide results more aligned with routine clinical practice.

On the other hand, the efficacy and safety of different durations of cytisinicline treatment are not compared to other drugs for the treatment of nicotine dependence, such as varenicline or nicotine replacement therapy. This is because this is not the ultimate goal of this study. However, such a comparative analysis will be carried out in subsequent studies. The selected patient population consists of smokers attending SCUs with high nicotine dependence and associated comorbidities and does not represent the general smoking population. This selection bias may influence the greater efficacy of extended cytisinicline treatment. However, these are units of varying complexity, and smoking cessation can also be addressed in individuals with less nicotine dependence.

Because this is a low-intervention clinical trial, smokers older than 65 years and those with serious psychiatric or cardiovascular comorbidities are not included. Therefore, we cannot generate scientific evidence on extended treatment in these vulnerable populations.

Abstinence outcomes are objectively determined during in-person visits using co-oximetry. However, other more precise methods, such as cotinine determination in body fluids, are not used. Nevertheless, this test is accepted as a powerful marker for verifying abstinence, establishing a carbon monoxide (CO in ppm) cutoff point of less than 10 ppm [27]. Although different monitors may vary in their sensitivity to CO, combining this measurement with patient self-reporting improves the predictive capacity of co-oximetry.

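### The planned correlation between CO-based and self-reported abstinence does not measure agreement; use a per-arm cross-table, and label the day 25, 50 and 75 outcomes as self-reported

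*Protocol article*

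**What the plan says.** Under Specific Outcomes Efficacy, sustained abstinence at 6 and 12 months is determined from CO readings. The next sentence adds a comparison with what participants say. Its first half names the statistic and the CO side: "The correlation between the sustained abstinence rate in each of the three arms studied at 6 and 12 months, based on co-oximetry results". Its second half gives the participants' side of the comparison: "the self-reported abstinence at 6 and 12 months will be calculated". No coefficient is named, and no measure of agreement or discordance is mentioned. Under Data Collection Variables, a participant counts as a nonsmoker when "their CO levels measured by co-oximetry are below 10 ppm", so the CO-based status is binary.

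The same outcomes section defines interval outcomes: "The abstinence rate will be analyzed from Day 25 to Day 50 in all 3 study groups and from Day 25 to Day 75". It also starts the relapse analysis at day 25, 50 or 75 according to arm. Table 3 gives the mode of those contacts: "Visit 5 (day 25; telephone"), "Visit 6 (day 50; telephone") and "Visit 7 (day 75; telephone"). It ticks co-oximetry only at the in-person visits (days 1, 7, 21, 90, 120 and 150; weeks 24, 48 and 52), while the participant's statement is ticked at every visit. The trial is open-label (Patient Enrollment and Randomization).

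**The concern.** When two yes/no classifications of the same people are compared, three things matter: how many self-reported abstainers fail the CO test, in which direction the two disagree, and whether this differs by arm. A correlation coefficient reports none of these directly. It can be high while self-report overstates abstinence, because over-reporting by smokers moves the self-reported rate one way only.

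This has some practical weight because self-report is the only source at days 25, 50 and 75. In an open-label trial whose arms stop drug at those different times, reporting could differ between arms. The comparison in Specific Outcomes Efficacy is the only planned analysis in the article that examines self-report against CO, so it should yield a usable number.

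**Working it through.** **Inputs.** CO-verified abstinence rates p come from Sample Size Determination: 30% (25 days), 45% in the text but .40 in the bracket (50 days), and 50% (75 days). The over-reporting fraction f is the share of CO-failing participants who say they are abstinent. The documents do not give it, so f = 5% to 50% is assumed, with no CO-verified abstainer reporting smoking. CO status is taken as the reference. The plan states no correlation or agreement figure, so there is none to reproduce.

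**Table cells.** Both abstinent: p. CO-failing but reporting abstinence: (1 − p)f. Both smoking: (1 − p)(1 − f). The self-reported rate is S = p + (1 − p)f.

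**Reading 1: correlation of the three arm-level rates.** With a common f, S = f + (1 − f)p. This is a straight line in p with positive slope, so the correlation is exactly 1.00 for any f below 100%. At f = 10% the self-reported rates are 37%, 50.5% and 55%; at f = 50% they are 65%, 72.5% and 75%. The correlation is 1.00 in both cases.

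With f differing by arm (A/B/C):
- 10/20/30%: self-reported rates 37%, 56%, 65%; correlation .997 (.999 with 40% in arm B). The C − A difference grows from 20 to 28 points.
- 30/20/10%: self-reported rates 51%, 56%, 55%; correlation .91 (.96 with 40% in arm B). The C − A difference shrinks from 20 to 4 points.

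**Reading 2: participant-level phi.** With these cells, phi = √[p(1 − f)/S]. For p = .30 and f = .10: √(.27/.37) = .854. Kappa for the same table: observed agreement .30 + .63 = .93; chance agreement .30 × .37 + .70 × .63 = .552; kappa = (.93 − .552)/(1 − .552) = .844. The false share of self-reported quits is (1 − p)f/S = .07/.37 = 18.9%.

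| f | p | S | Inflation (points) | phi | kappa | False share |
|---|---|---|---|---|---|---|
| 5% | .30 | .335 | 3.5 | .922 | .919 | 10.4% |
| 5% | .50 | .525 | 2.5 | .951 | .950 | 4.8% |
| 10% | .30 | .370 | 7.0 | .854 | .844 | 18.9% |
| 10% | .50 | .550 | 5.0 | .905 | .900 | 9.1% |
| 20% | .30 | .440 | 14.0 | .739 | .706 | 31.8% |
| 20% | .50 | .600 | 10.0 | .816 | .800 | 16.7% |
| 30% | .30 | .510 | 21.0 | .642 | .583 | 41.2% |
| 30% | .50 | .650 | 15.0 | .734 | .700 | 23.1% |
| 50% | .30 | .650 | 35.0 | .480 | .375 | 53.8% |
| 50% | .50 | .750 | 25.0 | .577 | .500 | 33.3% |

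Two things follow.
- For f of 5% to 20%, phi lies between about .74 and .95 while the self-reported rate is 2.5 to 14 points too high. Neither phi nor kappa shows the direction or the false share.
- Phi and the false share both depend on p as well as f. At f = 10%, phi is .854 for p = .30 and .905 for p = .50, and the false share is 18.9% against 9.1%, although reporting behaviour is the same. A by-arm difference in either needs the full table beside it.

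**Timing.** Months 6 and 12 correspond to the week 24 and week 52 visits, both in person with CO. No statistic from those visits directly checks a telephone statement at day 25, 50 or 75. The nearest visits with both measures are days 21 and 90, on either side of that window.

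**The case against.** A reader might infer that the correlation is meant to validate the telephone-based outcomes. The protocol does not say so. It lists the correlation as one calculation at 6 and 12 months, and Limitations runs the other way, claiming that "combining this measurement with patient self-reporting improves the predictive capacity of co-oximetry". The missing CO readings at days 25, 50 and 75 come from the visit schedule, not from the choice of statistic. An agreement table from in-person visits would not close that gap either.

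A reader might also infer that a correlation always looks reassuring. At participant level it does not: phi falls to .64–.73 at 30% over-reporting and .48–.58 at 50%. If calculated in each arm, it would also separate an arm with 10% over-reporting (.854 at p = .30) from one with none (1.00). Only the arm-level reading is blind to equal over-reporting. Nor would kappa solve the problem, as .844 against .854 shows.

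Finally, the main outcome is not reached: sustained abstinence at 6 and 12 months is stated to be CO-based. The article is condensed, names no coefficient, and may use the word loosely for concordance.

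All of this stands. What remains is that the article names a correlation, that one natural reading of it carries almost no information, and that the other omits the quantities of interest.

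**Conclusion.** The point holds as a low-cost improvement to a secondary analysis. A correlation is a poor summary of agreement between CO-based and self-reported abstinence: exactly 1.00 on arm-level rates under equal over-reporting, and about .74 to .95 at participant level while self-reported abstinence is inflated by 2.5 to 14 points. The participant-level range rests on assumed one-sided over-reporting of 5% to 20%, on CO-verified rates of 30% to 50%, and on CO status as the reference. The documents give no over-reporting figure, so these numbers show how the coefficient behaves; they do not predict bias in this trial.

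A separate and simpler point is that the day 25–50 and day 25–75 abstinence rates and the relapse start points rest on telephone statements without CO. That calls for a label, not for a conclusion that the outcomes are wrong.

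**What to change.** In Specific Outcomes Efficacy, replace the correlation with a table of CO status (below 10 ppm, or 10 ppm and above) by the statement taken at the same visit. Give it for each arm at each in-person follow-up visit: days 7, 21, 90, 120 and 150, and weeks 24, 48 and 52. From it report the share of self-reported abstainers with CO of 10 ppm or more, with a 95% CI, and the between-arm difference in that share. Because the share shifts with the abstinence rate, show the full counts, so that the fraction of CO-failing participants who claim abstinence can also be read off by arm. Kappa is not needed.

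Separately, state that the day 25–50 and day 25–75 rates and the day 25, 50 and 75 start points for relapse are self-reported and not CO-verified. Cite the day 21 and day 90 tables as indirect evidence only.

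The cost is one table in place of one coefficient and one sentence of labelling. Both measures are already scheduled at every in-person visit, so no new data are required.

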### Specific Outcomes (Safety)

The impact of morbidity and mortality in each treatment arm will be evaluated, as well as the percentage of side effects reported by participants, comparing their prevalence in each group throughout the study (1 year). The percentage of adverse effects at 25, 50, and 75 days will also be determined in participants, comparing their prevalence in each group.

Furthermore, the prevalence and severity of side effects for each regimen will be compared throughout the study (1 year).

Finally, the results of cardiac, hepatic, and renal variables will be compared between each group as indicators of treatment safety in each group at 25, 50, and 75 days of treatment and throughout the entire study period (1 year).

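### Weekly CO-based abstinence and the 1-year side-effect comparison do not match the visit calendar, and the ECG and laboratory time points fall on telephone contacts

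*Protocol article*

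**What the plan says.** **Efficacy outcomes.** Under Specific Outcomes Efficacy, "point abstinence will be analyzed every 7 days in each of the 3 arms studied, based on the results obtained in the CO tests". The Abstract also gives a seven-day frequency for point abstinence. Textbox 2 gives it twice, for the comparison of regimens and for the abstinence rate from day 25 to 6 months. The same efficacy section adds interval outcomes: "The abstinence rate will be analyzed from Day 25 to Day 50 in all 3 study groups and from Day 25 to Day 75".

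**Safety outcomes.** Specific Outcomes (Safety) looks at side effects, "comparing their prevalence in each group throughout the study (1 year"), and repeats the 1-year horizon for their prevalence and severity. It also sets cardiac, hepatic and renal results at days 25, 50 and 75. Textbox 2 sets ECG, liver-enzyme, electrolyte and renal abnormalities at baseline and on those same days.

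**Visit calendar.** Schedule of Participants presents Table 3 and Figure 1 as showing the visits and the "tests and quizzes to be carried out at each of the visits". The relevant columns read "Visit 5 (day 25; telephone"), "Visit 6 (day 50; telephone"), "Visit 7 (day 75; telephone") and "Visit 8 (day 90; in person"). The Limitations section confirms that CO is measured at in-person visits. Data Collection Variables, however, says that co-oximetry confirms abstinence at every participant visit.

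**The concern.** An outcome defined by a CO test on a weekly grid needs a CO test on that grid, or at least near it. If the calendar does not provide one, the analysis has to substitute self-report or silently use a different set of time points. Neither choice is described.

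The timing makes this worse. The arms receive the same treatment to day 25 and differ only after that, so the interval rates from day 25 are where an effect of longer treatment would first appear. Participants know their arm, and self-report without biochemical confirmation can be influenced by that knowledge.

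On safety, the trial's hypothesis includes no increase in adverse events with longer treatment. A comparison described as covering 1 year, but fed by enquiries that end at day 75, would be read as stronger evidence than it is.

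**Working it through.** There is no calculated figure in the plan to reproduce; the check sets the stated outcomes against Table 3. Tick marks were assigned to the 14 visit columns by their position in the extracted table, and every tick fell on a visit column. Weeks are converted as week × 7 days.

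| Visit | Day | Mode | CO | Adverse events |
|---|---|---|---|---|
| 1 | 1 | in person | yes | no |
| 2 | 7 | in person | yes | yes |
| 3 | 14 | telephone | no | yes |
| 4 | 21 | in person | yes | no |
| 5 | 25 | telephone | no | yes |
| 6 | 50 | telephone | no | yes |
| 7 | 75 | telephone | no | yes |
| 8 | 90 | in person | yes | no |
| 9 | 120 | in person | yes | no |
| 10 | 150 | in person | yes | no |
| 11 | 168 (week 24) | in person | yes | no |
| 12 | 252 (week 36) | telephone | no | no |
| 13 | 336 (week 48) | in person | yes | no |
| 14 | 364 (week 52) | in person | yes | no |

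**Step 1: weekly CO.**
- The grid is day 7, 14, 21 and so on: 168/7 = 24 points to week 24 and 364/7 = 52 points to week 52.
- CO tests on the grid to week 24: days 7, 21 and 168, so 3 of 24. To week 52, days 336 and 364 are added, so 5 of 52.
- A more generous count lets a CO test within 3 days stand for a grid point. Day 90 then serves day 91, day 120 serves day 119, and day 150 serves day 147. This gives 6 of 24 and 8 of 52.
- Self-report is recorded at all 14 visits. It falls exactly on the grid at days 7, 14, 21, 168, 252, 336 and 364, so 7 of 52. It is not weekly either.

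**Step 2: the early gap.**
- 90 − 21 = 69 days without CO.
- Nine weekly points (days 28, 35, 42, 49, 56, 63, 70, 77 and 84) lie inside it. The last is 90 − 84 = 6 days from the next test, so even the generous count recovers none of them.
- By the Trial Design text, the extra treatment runs for 25 days after day 25 in arm B (to day 50) and for 50 days in arm C (to day 75). Both lie wholly inside the gap. The last arm C row of Table 1 stops at day 50, which needs reconciling with that text, but the gap covers the extension on either reading.
- A second gap runs from week 24 to week 48: 336 − 168 = 168 days.

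**Step 3: interval rates.** Days 25, 50 and 75 are all telephone contacts where only the participant's statement is ticked. No CO value exists at either end of, or inside, the day 25-50 and day 25-75 windows.

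**Step 4: adverse events.** The last scheduled enquiry is day 75. Uncovered follow-up is 364 − 75 = 289 days, and 289/364 = 0.794, or 79%. Textbox 2 independently ends its adverse-event list at day 75. Scheduled observation after the end of treatment is 75 − 25 = 50 days in arm A, 75 − 50 = 25 in arm B and 75 − 75 = 0 in arm C.

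**Step 5: ECG and laboratory.** Days 25, 50 and 75 against the in-person days above: none coincides, and the nearest are days 21 and 90.

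**The case against.** Several points on the other side are sound, and they limit how far this goes.

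- **Interval rates.** A reader might infer that these would be reported as CO-based. The article ties CO to sustained and point abstinence, not to the interval rates, and Limitations speaks of combining CO at in-person visits with self-report. The rates can be computed from the participants' statements. What stands is that their basis is not stated.
- **ECG and laboratory results.** A reader might infer that these cannot be obtained. That does not follow. Table 3 as shown has no ECG or laboratory row at any visit, baseline included, and no withdrawal or craving row, so it is not a complete list of procedures. Separate attendances may be planned in the full protocol. What stands is that the outcome days carry a telephone label and the two places need reconciling.
- **Adverse events.** A reader might infer that nothing is known about safety after day 75. Pharmacovigilance sets no such cut-off, handling of events is in an appendix that is not shown, and access to medical histories is foreseen, so serious events, morbidity and mortality may still be captured. These sources would not give the prevalence of side effects by a common enquiry. The unequal post-treatment windows do not make the comparisons at days 25, 50 and 75 unfair, because all arms share the same window from the start of treatment.
- **Main efficacy assessments.** A reader might infer that the efficacy outcomes as a whole fail. They do not: sustained abstinence at 6 and 12 months has CO in weeks 24 and 52.

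**Conclusion.** The mismatch is real but bounded, and should be corrected.

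- **CO-based point abstinence at seven-day intervals** contradicts the calendar. On exact matching 3 of 24 weekly points to week 24 and 5 of 52 to week 52 have a test, and on the generous count 6 and 8. The 69-day gap sits over the whole period in which the arms differ in treatment.
- **The day 25-50 and day 25-75 rates** are self-reported by telephone under open-label conditions, without being labelled as such.
- **The 1-year side-effect comparison** has no scheduled enquiry behind it for 79% of follow-up.
- **The ECG and laboratory days** conflict with the telephone labels. This supports reconciliation only.

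The conclusion assumes that the ticks of Table 3 were read into the right columns, which the mode labels support: every CO tick falls on an in-person visit. It also assumes that no further CO tests or adverse-event enquiries are scheduled outside that table. Textbox 2 supports this for adverse events.

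**What to change.** 1. In the Abstract, Specific Outcomes Efficacy and Textbox 2, replace the seven-day wording with point abstinence (CO below 10 ppm plus self-report) at the scheduled post-baseline CO visits: days 7, 21, 90, 120 and 150 and weeks 24, 48 and 52. Correct the statement in Data Collection Variables that CO confirms abstinence at every visit, since 5 of the 14 are by telephone.
2. Label the day 25-50 and day 25-75 rates as self-reported, and name day 90 as the first CO verification after treatment.
3. Add the adverse-event question to visits 8 to 14, or limit the side-effect comparison to day 75 and say so.
4. Reconcile the ECG and laboratory time points with the visit calendar.

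The cost is mostly wording, plus one question at seven contacts that already take place. The downside is that fewer CO-verified time points can be claimed, and the day 21-90 gap is declared rather than closed. According to Results, the first preselected patients had not yet had their initial visit at the time of writing, so at that stage the collection of adverse events could still be changed. Side effects that are never asked about cannot be recovered later.

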**Methods:**

A prospective, multicenter, open-label, controlled, parallel, phase IV clinical trial of 402 smoker patients prepared to quit smoking. The study was conducted in 10 hospitals in Spain. A control group is compared to 2 intervention groups in which the duration of the drug is increased without increasing its dose, administering half and all, respectively, of an additional marketed container that includes 100 tablets. Thus, participants will be randomized to three groups in a 1:1:1 ratio to receive cytisinicline: (1) a control group treated with cytisinicline according to the usual clinical guidelines and product information (25 days); (2) a group with a 50-day cytisinicline regimen (an additional 25 days at a dose of 1.5 mg every 12 hours), seeking to increase its efficacy while minimally impacting adherence; and (3) a group with a 75-day regimen (an additional 50 days at a dose of 1.5 mg every 12 hours), attempting to increase its efficacy, although the longer duration of the drug may threaten adherence. Efficacy in the 3 arms will be analyzed through sustained abstinence at 6 and 12 months, point abstinence rate assessed every 7 days, and abstinence rate from Day 25 to Day 50 and from Day 25 to Day 75 in the 3 study arms. (1) The variation in withdrawal and craving symptoms in the 3 groups, (2) safety through the percentage of adverse events in the 3 treatment arms, and (3) economic impact by evaluating the cost-effectiveness and cost-utility ratios of the 2 prolonged regimens versus the usual clinical cytisinicline regimen. To calculate the differences between the 3 groups for each outcome variable, a univariate analysis will be performed. Statistically significant variables will be included in a multivariate model.

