## Methods

### Trial Design

Phase IV randomized, open-label, controlled, parallel, multicenter clinical trial in patients who are candidates for smoking cessation to demonstrate the superiority of maintenance therapy with cytisinicline compared to the standard regimen.

The trial was designed according to the standardized guide for interventional trial protocols, SPIRIT (Standard Protocol Items: Recommendations for Interventional Trials statement [Multimedia Appendix 2]). A total of 402 patients from 10 smoking cessation units in Spain will be randomized. Recruitment will last for one year, with a follow-up of 52 weeks per patient recruited. Candidate patients who sign the informed consent form will be randomized to 3 possible arms in a ratio of 1:1:1.

Arm A: control group. Participants randomized to this group will be treated with cytisinicline as stated in the data sheet. They must remain smoke-free from day 5 of treatment.

Arm B: maintained therapy 1. Following the standard regimen, these patients will maintain treatment for an additional 25 days at a dose of 1.5 mg twice daily.

Arm C: maintained therapy 2. Following the standard regimen, these patients will maintain treatment for an additional 50 days at a dose of 1.5 mg twice daily (see Table 1).

At the end of the treatments, participants will continue in the follow-up phase, without treatment, until completing 52 weeks in the study (see Figure 1).

**Table 1 table1:** Dosage guidelines in each of the 3 treatment arms.

Days of treatment		Recommended dosage	Maximum daily dose	Recommendations	

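### Up to day 50 the prescribed regimens differ only between stopping (A) and continuing (B and C), so three-group comparisons are valid but give away precision that a pooled B+C versus A contrast would recover

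*Protocol article*

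**What the plan says.** **Regimens (Trial Design and Table 1).** Of arm A the article says "Participants randomized to this group will be treated with cytisinicline as stated in the data sheet", which means 25 days. After that same course, arm B patients continue: "these patients will maintain treatment for an additional 25 days at a dose of 1.5 mg twice daily". For arm C, "these patients will maintain treatment for an additional 50 days at a dose of 1.5 mg twice daily". Table 1 gives identical rows for all arms to day 25, and identical rows for B and C on days 26-50.

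**Comparisons.** The Methods paragraph of the abstract sets a general rule: "To calculate the differences between the 3 groups for each outcome variable, a univariate analysis will be performed". Under Specific Outcomes Efficacy, "The abstinence rate will be analyzed from Day 25 to Day 50 in all 3 study groups", and for the withdrawal scale (MNWS) and craving, "their change from this visit will be measured on days 25, 50, and 75 in all 3 study arms". Under Specific Outcomes (Safety), "The percentage of adverse effects at 25, 50, and 75 days will also be determined in participants, comparing their prevalence in each group". Cardiac, hepatic and renal results are compared between groups at the same days.

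The article does not mention combining B and C up to day 50, and it does not rule this out.

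**The concern.** Until day 50 there are two prescribed exposures, not three. On days 1-25 no arm differs from another in the tablets prescribed. On days 26-50 A is off drug while B and C are on the same schedule.

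The day 25-50 window bears directly on the trial's rationale, because the Introduction rests it on relapse and craving soon after a 25-day course. In that window the question is whether continuing beats stopping. A pairwise comparison of A with B (or C) uses only half the patients who continued. A three-group test uses all of them, but spends one of its two degrees of freedom on B versus C, where no difference in prescribed drug exists.

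There is also a point of interpretation. A difference between arms at day 25, or between B and C up to day 50, cannot come from extra prescribed tablets. The article does not say how such a difference should be read.

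**Working it through.** **Inputs.** From Sample Size Determination: 110 per arm before losses; 402 in total, so 402/3 = 134 per arm; 5% significance (taken as two-sided); control rate 30%. The intermediate-arm rate is printed as 45% in words and .40 in symbols, so both are used. These are the plan's sustained-abstinence rates. Using them for day 50 is an assumption, because no day-50 rate is given.

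**The plan's own figure.** A three-group chi-square test (2 df, 80% power) with 30/45/50% needs 109 per arm, against 110 stated. With 30/40/50% it needs 116. The total follows as 110 × 1.21 = 133.1, rounded up to 134, and 134 × 3 = 402. The stated size therefore matches a three-group test on long-term abstinence. No power is stated for day-50 outcomes.

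**Precision.** For a common rate p and n per arm:
- A versus B: SE = √[p(1−p)(1/n + 1/n)]
- A versus B+C: SE = √[p(1−p)(1/n + 1/(2n))]
- Ratio = √(1.5/2) = 0.866, a 13% reduction whatever p and n are.

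At n = 134 the 95% interval half-width falls from 11.0 to 9.5 points at p = 0.30, from 11.7 to 10.2 at 0.40, and from 12.0 to 10.4 at 0.50.

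**Power, 30% versus 45%, n = 134.**
- A versus B: null SE √(2 × 0.375 × 0.625/134) = 0.0591; alternative SE √[(0.21 + 0.2475)/134] = 0.0584; z = (0.15 − 1.96 × 0.0591)/0.0584 = 0.58; power 72%.
- Three groups: noncentrality 134 × (0.10² + 0.05² + 0.05²)/(0.40 × 0.60) = 8.375; power 74%.
- A versus B+C: null SE √(0.40 × 0.60 × 1.5/134) = 0.0518; alternative SE √(0.21/134 + 0.2475/268) = 0.0499; z = (0.15 − 1.96 × 0.0518)/0.0499 = 0.97; power 83%.

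**Range over the assumptions (B and C equal).**

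| n per arm | Rates | A v B | Three-group | A v B+C |
|---|---|---|---|---|
| 134 | 30% v 45% | 72% | 74% | 83% |
| 110 | 30% v 45% | 63% | 65% | 75% |
| 134 | 30% v 40% | 40% | 40% | 50% |
| 134 | 40% v 50% | 38% | 38% | 47% |

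**If B and C are not equal at day 50.** The pooled contrast estimates the average of the two arms. With A 30%, B 45%, C 40% and n = 134, the pooled rate is (45 + 40)/2 = 42.5%. Then null SE = √(0.3833 × 0.6167 × 1.5/134) = 0.0514, alternative SE = √(0.21/134 + 0.2444/268) = 0.0498, z = (0.125 − 1.96 × 0.0514)/0.0498 = 0.49, and power is 69%. The three-group noncentrality is 134 × (0.0833² + 0.0667² + 0.0167²)/0.2364 = 6.61, power 63%, and A versus B stays at 72%. A gap of this size already removes the advantage over A versus B.

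**Error rate.** In simulation with equal true rates, one three-group test rejects about 5% of the time, and so does the pooled contrast.

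**The case against.** The strongest reply is that nothing here is wrong. Comparing arms as randomised is the safe default, these are supporting outcomes, and the choice of contrast is often left to an analysis plan, which is not shown. The Outcomes section frames the trial as maintained therapy against the standard regimen, which already fits an A versus B+C contrast. All of this stands, and it is why the point is only an improvement.

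The second reply is that identical prescriptions are not identical exposure. The trial is open-label, and the abstract itself expects the 75-day regimen to put adherence at more risk than the 50-day one. Knowing the assigned length could change behaviour or reporting before day 50. This stands too. Pooling should therefore sit beside the by-arm results and not replace them, and the early between-arm results have value as a check.

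A reader might go further and infer three things that the article does not support:
- *That the day 25-50 comparison is between identical arms.* It is not. A is off drug and B and C are on it, so A against either is a genuine contrast. Only B versus C lacks a difference in prescribed drug.
- *That the three-group comparison breeds false regimen effects.* A single three-group test keeps its 5% error. Three unadjusted pairwise tests would raise it to about 12%, but the article does not specify them for these outcomes.
- *That day-25 comparisons should be removed.* They cannot show a duration effect, but in an open-label trial they can show anticipation or reporting effects.

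**Conclusion.** The point holds as a modest loss of precision, not as an invalid analysis. Up to day 50, A versus pooled B+C is a randomised comparison that addresses continuing versus stopping with a standard error 13% smaller than A versus B. Under an assumed 30% versus 45% at 134 per arm, power is 83% instead of 74% (three-group) or 72% (A versus B). Over the other scenarios tabulated with equal B and C rates, the gain is about 8 to 12 points.

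These figures rest on borrowed rates, a two-sided 5% level and little anticipation effect of the assigned length. At day 25 pooling brings no gain, because there is no prescribed regimen contrast to estimate; the issue there is interpretation only. Sustained abstinence at 6 and 12 months, where all three regimens differ, is unaffected. Table 1 and the text disagree on arm C after day 50. They must be reconciled, but this does not touch the present point.

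**What to change.** Before any outcome data are seen, add to the analysis wording:

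1. For outcomes up to day 50 (abstinence from day 25 to 50; MNWS, craving, adverse effects, ECG and laboratory results at day 50), prespecify pooled B+C versus A as the contrast for continuing versus stopping. Report it together with the results for each arm.
2. Keep the between-arm results at day 25 and the B versus C results up to day 50. Label them as checks on open-label anticipation or reporting, and state that they are not evidence of a duration effect.
3. Leave the later comparisons as three-arm comparisons.

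The cost is a few sentences; no extra patients, visits or data are needed. The downside is that the pooled contrast is an average over B and C, and its gain shrinks or disappears if the assigned length already changes behaviour before day 50. The by-arm results let the reader see whether that happened.
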